## Abstract

**Background:**

Running is associated with desirable lifestyle changes. Therefore several initiatives have been undertaken to promote running. Exact data on the health effects as a result of participating in a short-term running promotion program, however, is scarce. One important reason for dropout from a running program is a running-related injury (RRI). The incidence of RRIs is high, especially in novice runners. Several studies examined potential risk factors for RRIs, however, due to the often underpowered studies it is not possible to reveal the complex mechanism leading to an RRI yet.

The primary objectives are to determine short- and long-term health effects of a nationwide “Start to Run” program and to identify determinants for RRIs in novice runners. Secondary objectives include examining reasons and determinants for dropout, medical consumption and economical consequences of RRIs as a result of a running promotion program.

**Methods/design:**

The NLstart2run study is a multi-center prospective cohort study with a follow-up at 6, 12, 24 and 52 weeks. All participants that sign up for the Start to Run program in 2013, which is offered by the Dutch Athletics Federation, will be asked to participate in the study.

During the running program a digital running log will be completed by the participants every week to administer exposure and running related pain. After the running program the log will be completed every second week. An RRI is defined as any musculoskeletal ailment of the lower extremity or back that the participant attributed to running and hampers running ability for at least one week.

**Discussion:**

The NLstart2run study will provide insight into the short- and long-term health effects as a result of a short-term running promotion program. Reasons and determinants for dropout from a running promotion program will be examined as well. The study will result in several leads for future RRI prevention and as a result minimize dropout due to injury. This information may increase the effectiveness of future running promotion programs and will thereby contribute positively to public health.

**Trial registration:**

The Netherlands National Trial Register NTR3676. The NTR is part of the WHO Primary Registries.

## Background

Several initiatives have been undertaken to encourage people to start running. In the Netherlands a nationwide supervised running promotion program called Start to Run is offered by the Dutch Athletics Federation, which attracts over 8,000 novice runners annually. So far, the exact health benefits of a 6-week running promotion program and reasons for dropout have barely been examined (Van Merode T, Vasse R, Twellaar M, Hartgens F: Positive healthy lifestyle changes: high compliance and adherence to exercise in training programmes for novice sporters (start-to-run and start-to-walk); 6 weeks and 6 months follow-up, submitted).

Running is associated with desirable lifestyle changes such as weight loss, smoking cessation and improvement in cardio respiratory fitness and mental health [1-3].The health benefits associated with a short-term promotion program for novice runners, however, have not yet been examined. Effectiveness of such a program increases the possibilities to improve public health.

Preliminary dropout from a running promotion program hinders a shift from extrinsic motivation to intrinsic motivation, which is important in becoming a regular exerciser [4]. An important dropout reason from these programs is the occurrence of a running-related injury (RRI) [1]. Consequently, sustaining an RRI is associated with failure to start and maintain a physically active lifestyle [5]. Moreover, research has shown that especially novice runners are at a high risk for sustaining an RRI [6-8]. Prevention of RRIs in novice runners is therefore of particular importance. Prevention of RRIs in novice runners participating in a running promotion program is especially important to minimize medical costs associated with RRIs and to maximize the positive health effects by maintaining an active lifestyle [1,9]. From this perspective it is also important to identify other reasons besides RRIs for dropout from a start-to-run program.

Several studies tried to identify determinants for RRIs. One of the reasons that the most important risk factors for RRIs have not yet been identified might be related to the often-underpowered studies performed. Since the development of an RRI results from a complex interaction between both intrinsic and extrinsic risk factors, a multivariate analysis is essential for identifying risk factors for RRIs [10,11]. Multivariate methods are susceptible to producing problematic results if too few RRIs are available relative to the number of risk factors analyzed in the model. As a result, several studies that used this type of analysis first examined the independent link of potential risk factors with RRIs and only factors univariately associated with an RRI were entered into the multivariate model [7,12-14]. To account for the multifactorial nature of RRIs this univariate selection of potential risk factors is undesirable [15]. A large cohort study would increase the number of factors that can be entered into a multivariate model and therefore reduce the need for a univariate selection, hence it is needed for identification of risk factors for general and specific RRIs which is important for the development of preventive measures.

The primary objectives of the NLstart2run study are therefore to determine short- and long-term health effects of a nationwide “Start to Run” program and to identify determinants for RRIs in novice runners. This information is important for developing successful running promotion programs in the future [16]. Secondary objectives are to determine reasons and determinants for dropout from a supervised running promotion program, and to identify the course and medical consumption of injured runners and the associated costs. In this article we describe the protocol of the prospective cohort study NLstart2run.

## Methods/design

### Study design

The NLstart2run study is a multi-center prospective cohort study with a follow-up at 6, 12, 24 and 52 weeks, as can be seen in Figure 1. The study design, procedures and informed consent procedure were approved by the Medical Ethics Committee (no. 2012/350) of the University Medical Center Groningen (UMCG), the Netherlands. The trial is registered in the Netherlands Trial Registry (NTR3676).

**Figure 1 F1:**
[figure not shown]
Flowchart of the NLstart2run study.

### Study population

All participants that sign up for the 6-week Start to Run (STR) program of the Dutch Athletics Federation in 2013 will be asked to participate in the NLstart2run study. The STR course is organized twice a year and starts in March and September. The STR participants will be recruited by the Dutch Athletics Federation via national and local media. Additional information about the study and procedures is sent to all STR participants. Participants can register for the study after signing a digital informed consent.

#### ***Inclusion & exclusion criteria***

Participants of the STR program who are aged between 18 and 65 are eligible for inclusion. Participants will be excluded if there are absolute contraindications for vigorous physical activities according to the American College of Sports Medicine ACSM) guidelines [17], or in case of unwillingness to keep a running log.

### The STR training program

The STR training program consists of three training sessions per week, one group training session supervised by a licensed athletic trainer and two individual training sessions. Each training session begins with a 15-minute warm-up and finishes with a 15-minute cool-down that consist of walking, stretching and relaxation exercises. The core of the training includes running program in which both running duration and intensity will be gradually increased. The STR program aims to prepare participants in 6 weeks for a 20-minute run without breaks. After the 6-week STR program, participants can choose to continue running in a way they prefer.

### Injury definition

In the current study a running-related injury (RRI) is defined as any musculoskeletal ailment of the lower extremity or back that the participant attributed to running and hampers running ability for at least one week [14,18]. Hampering of running can be either a reduction in running speed, distance or duration, or an inability to run, both as a result of running-related pain.

### Sample size

Based on previous studies on RRIs among novice runners, an injury incidence of 20% is expected [7,14,18]. Taking into account a dropout rate of 20% [6,7,14,18,19], the inclusion of 6,000 participants will lead to approximately 4,800 participants at follow-up. With an RRI incidence of 20%, a total of 960 RRIs are expected. Taking into account the need of a minimum of 10 RRIs per risk factor analyzed in a multivariate model, this is sufficient for accounting for the multivariate nature of RRIs [15,20].

### Measurements

#### ***Baseline questionnaire***

The five-part baseline questionnaire will be administered online after participants give informed consent. Demographics, anthropometrics, and other personal characteristics are covered in part 1. Self-reported body height and weight will be used to calculate BMI (weight (kg) / height^2^ (m)).

Part 2 covers information on previous running and sports participation [21,22]. Also information about previous injuries during running (“Have you ever had a running injury?”) and musculoskeletal complaints in other sports (“Have you ever had complaints in your bones, joints or muscles and tendons during sports and exercise?”) are obtained per anatomical site. Information on footwear and insoles is obtained in the second part as well.

Physical activity during daily life is assessed in part 3 with the Short Questionnaire to Assess Health-enhancing physical activity (SQUASH). The SQUASH was designed to give an indication of habitual activity level during an ordinary week. The SQUASH has been tested for validity and reliability with an accelerometer as a criterion measure in a general adult population and has turned out to be reliable and valid [23,24].

In part 4, the Behavioral Regulation in Exercise Questionnaire-2 (BREQ-2) is used to measure motivation toward exercise in general. The BREQ-2 assesses a motivation and external, identified, interjected and intrinsic regulations, and showed sufficient validity in adults [25].

In the final part physical, mental and social health is measured. Perceived health is assessed with the Dutch version of the RAND-36 Health Survey (RAND-36), which was translated from the standardized SF-36 Health Survey [26,27]. The RAND-36 is a validated and reliable measure [26]. Mastery as part of mental health is measured using the 7-item scale of Pearlin and Schooler [28]. Physical health is measured with a 5-item scale on high prevalent health complaints, and social health is measured with the shortened 6-item scale for loneliness [29,30].

#### ***Follow-up questionnaires***

The runners starting with the STR program in March 2013 will receive four follow-up questionnaires at 6, 12, 26 and 52 weeks after beginning with the program. The group of runners who start in September will only receive three follow-up questionnaires at 6, 12 and 26 weeks. In the follow-up questionnaires continuation and reasons for discontinuation of running will be monitored. Participation in other sports will also be monitored in the follow-up questionnaires. Besides questions about continuation of running or other sport activities, all follow-up questionnaires also measure physical activity (SQUASH), motivation toward exercise (BREQ-2), and physical and mental health (RAND-36, 7-items scale of Pearlin and Schooler, 5-item scale on high prevalent health complaints, and shortened 6-item scale for loneliness).

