### Statistical analyses

Incidence of RRIs will be calculated for all participants and for male and female participants separately as the number of new injuries reported per 1000 hours of running exposure. Exposure time (in hours of running exposure) will be calculated from the time the participant started the running program until an RRI is reported (injured runners) or until the end of the program (non-injured runners).

Descriptive data will be presented as means (± s.d.) and frequency distributions.

For identification of risk factors for RRIs only data from the baseline questionnaire and the running log will be used. Data of the follow-up questionnaires will not be used for this purpose, because these data do not contribute to a pre-running risk-profile. It is possible for a single subject to sustain multiple RRIs during the study period. In this case only the occurrence of the first RRI will be used for analysis. Potential risk factors for RRI will be entered into a multivariate Cox regression prediction model. Hazard ratios and the corresponding 95% confidence intervals will be calculated for the factors associated with RRI.

Data of the baseline and follow-up questionnaires will be compared with a repeated-measures ANOVA to examine the health effects of participating in a supervised running program. Reasons for dropout from the start-to-run program will be described and determinants for dropout will be analyzed by multivariate logistic regression models. Course and medical consumption and the associated direct and indirect costs will be described for injured runners.

Missing data will be completed by multiple imputation using the Multiple Imputation by Chained Equations (MICE) procedure, a technique in which missing values are replaced based on estimated relations in the dataset [37]. Ten multiple imputed datasets are generated, whereupon the results of those ten multiple imputed datasets will be combined using the rules given by Rubin [37].

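### The week-52 questionnaire goes to March starters only, but the repeated-measures ANOVA and the imputation rule make no exception for it, and the mid-term visit is given as both week 24 and week 26

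*Protocol article*

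**What the plan says.** The Study design section, like the Abstract, describes a "multi-center prospective cohort study with a follow-up at 6, 12, 24 and 52 weeks". Neither place distinguishes between start groups.

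The Follow-up questionnaires section differs in two ways. It schedules the third questionnaire at week 26 rather than week 24, for both waves. It also gives the week-52 questionnaire to March starters alone: "The group of runners who start in September will only receive three follow-up questionnaires at 6, 12 and 26 weeks".

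The Statistical analyses section fixes the method for the health effects: "Data of the baseline and follow-up questionnaires will be compared with a repeated-measures ANOVA". It then states that missing data are to be completed by MICE and combined by Rubin's rules: "Ten multiple imputed datasets are generated". It names no analysis set for week 52. It does not separate scores that were never requested from scores lost to non-response.

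**The concern.** Long-term health effects are part of a primary objective, and week 52 is the latest questionnaire. For September starters that occasion is absent by schedule, yet the imputation rule as worded covers any missing value.

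If the rule is applied to all occasions, every September week-52 score is generated from the March wave. No September starter supplies a week-52 value, so a difference between waves at week 52 cannot be estimated from the data. The imputation model would have to assume how the September wave behaves there. A week-52 result labelled as covering all participants would then carry direct information on one wave only.

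Separately, the 24 versus 26 week discrepancy leaves the timing of the mid-term assessment unclear.

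**Working it through.** **Inputs from the document**
- Planned inclusion and retention (Sample size): "the inclusion of 6,000 participants will lead to approximately 4,800 participants at follow-up".
- Dropout (Sample size): 20%, not tied to a time point.
- Start months (Study population): March and September. The number expected in each wave is not given.
- Week-52 questionnaire (Follow-up questionnaires): March starters only.

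**The plan's own figures.** 6,000 × (1 − 0.20) = 4,800, and 4,800 × 0.20 = 960 injuries. Both reproduce exactly. They belong to the injury model and are not affected by this point.

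**Week-52 availability.** Two assumptions are needed: a March share *s*, and that the 20% dropout applies at week 52.
- Never asked at week 52: 6,000 × (1 − *s*)
- Observed at week 52: 6,000 × *s* × 0.80
- Share of the 6,000 imputed if MICE is applied to all: 1 − 0.80*s*

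| March share *s* | Never asked | Observed | Imputed share |
|---|---|---|---|
| 30% | 4,200 | 1,440 | 76% |
| 40% | 3,600 | 1,920 | 68% |
| 50% | 3,000 | 2,400 | 60% |
| 60% | 2,400 | 2,880 | 52% |
| 70% | 1,800 | 3,360 | 44% |
| 80% | 1,200 | 3,840 | 36% |

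The imputed share is above one half only when 1 − 0.80*s* > 0.50, that is when *s* < 0.625.

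**Season.** Counting from the start months, week 26 falls around September for the March wave and around March for the September wave. The March wave's change from week 26 to week 52 therefore runs from autumn to spring. The September wave's would run from spring to autumn. Imputation would carry the first pattern over to the second group. The SQUASH asks about habitual activity in an ordinary week, which could plausibly vary with season.

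**The case against.** The strongest reply is that the statistical text does not say what it seems to imply. It does not specify one five-occasion model, one whole-cohort set, or imputation of September week-52 scores. A March-only comparison at week 52 would fit the wording, and the full protocol or analysis plan, not shown, may say so. The list of follow-up weeks can be read as the study's occasions rather than as a promise to every participant, and the questionnaire section discloses the restriction openly. This stands in part: that all occasions are treated as collected for all is an inference from unrestricted wording. But the article does fix the method and an imputation rule without exceptions, and these do not fit the schedule it also fixes.

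A score absent by schedule is not driven by participant behaviour, so the main cost may be precision and dependence on the imputation model. That is fair. Seasonal bias is possible but not shown. Nor does the article define long-term as week 52, and both waves are measured at week 26.

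Four stronger readings are tempting, and the document does not support them:
- A reader might infer that most week-52 scores would be imputed, or that half the cohort is affected. Both depend on a split that is not stated.
- A reader might infer that the ANOVA would discard all September starters. That is a complete-case analysis, and the plan specifies imputation instead.
- A reader might take the 4,800 as an overstated week-52 number. It supports the injury model, makes no claim about week 52, and is arithmetically correct.
- A reader might conclude that ten imputed datasets are too few. That depends on the fraction of missing information, which the document does not give and which the earlier questionnaires could lower.

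Finally, preferring a mixed model to ANOVA with MICE is partly a matter of taste, since both rest on a missing-at-random assumption. The firmer reason here is that a mixed model does not need a value at every occasion for every participant.

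**Conclusion.** The point holds in this form. The follow-up schedule contradicts itself on week 24 versus week 26, and week 52 is listed without restriction in one place and for March starters only in another. The analysis and imputation rules take no account of that restriction. Applied as written to all occasions, they would make the week-52 part of a primary objective rest partly on generated scores for a non-randomised wave with no week-52 data.

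The size depends on two assumptions: the March share and 20% dropout at week 52. At an equal split, 60% of week-52 scores would be imputed, and for March shares of 30% to 80% the figure runs from 76% to 36%. Even at 80%, 1,200 participants are never asked. The contradiction and the mismatch between schedule and analysis need neither assumption. The matter should be settled before the health outcomes are analysed.

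**What to change.** 1. Reconcile week 24 with week 26 in the Abstract, Study design and Follow-up questionnaires sections.
2. State in the design text that week 52 applies to March starters only.
3. Estimate and report the week-52 health effect for March starters only, labelled as such.
4. Restrict MICE to scheduled questionnaires, so that no September week-52 score is generated.
5. Analyse the health outcomes with a linear mixed model on all available scheduled occasions. Include time as a category and start wave, with wave-by-time terms for the occasions both waves share. A wave-by-week-52 term must be left out, because the September cell is empty.

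This needs changes of wording and model only, and no new data. The cost is that the 52-week conclusion covers March starters alone and its interval will be wider than that of an imputed whole-cohort estimate.

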#### ***Web-based training log during the 6-week STR program***

During the 6-week STR program a weekly training log is sent to the participants. For each training session, data on running exposure (frequency and duration), running surface, perceived exertion and pain is registered. Weekly information on other sports activities (type of sports and exposure that week) is obtained from the training log. When participants do not enter their digital training log after five days, an e-mail reminder is sent automatically.

Perceived exertion will be assessed using Borg’s Ratings of Perceived Exertion (RPE) scale. The RPE scale is widely used in exercise science and sports medicine to monitor or prescribe levels of exercise intensity. Borg’s RPE scale has shown to be a valid measure of exercise intensity [31].

Pain will be measured by registering anatomical site of the body and severity of pain for each training session. A mannequin will be shown to identify the anatomical site of the running-related pain. By clicking on the anatomical site, the same spot will be pointed red. Severity of pain is additionally subdivided into pain without limitations, pain that causes a restriction in running, and pain which makes running impossible. To classify the severity of pain, a Visual Analog Scale (VAS) is used. When a training session is skipped, the reason for it will be asked (running-related pain, other pain, illness, motivation, or other reason). When running-related pain is the reason, anatomical site and severity of pain will be obtained.

In addition to the pain registration obtained for each training session, the development and progression of overuse injuries is also monitored with a new method as proposed by Clarsen et al. [32]. This method is designed to monitor overuse problems for predefined anatomical locations separately. In the current study, however, this is not ideal because all injury locations are of interest. The proposed method has thus been modified: instead of monitoring pain for each predefined anatomical location, general data is collected and the specific anatomical location is asked for afterwards.

#### ***Web-based training log after the 6-week STR program***

After the 6-week STR program, a digital training log is sent to the participants every two weeks. This training log is a simplified version of the log that was used during the first six weeks. Information on running exposure, running surface, running-related pain and other sports activities is registered per week instead of at each training session. In this simplified training log, pain registration and monitoring of overuse injuries is similar to the methods used in the first six weeks. Participants who quit running after the STR program can indicate so, and only have to complete the information on other sports activities.

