#### ***Questionnaire for injured runners***

When an RRI is registered in the web-based training log, a questionnaire will be automatically sent to the participant after two weeks. This questionnaire is used to specify medical/paramedical treatment, the order of treatments, type and frequency of the treatment, medical aids, and absence from work, school or training due to the RRI. Injured runners are asked to specify the injury location, if the injury is new or recurrent, what structure is injured (e.g. muscle, tendon, bone or ligament), and the injury mechanism (e.g. strain, sprain, rupture, dislocation, contusion, inflammation or overuse). When the runner is seen by a professional, a diagnosis will be asked. Until recovery from the RRI, every four weeks a follow-up questionnaire on medical/paramedical consumption and absence from work, school or training is sent to the injured runner.

To validate the RRI registration method that is used in this study, approximately 10% of the subjects who sustain an RRI will be contacted by a sports physician. The sports physician will perform a standard physical examination and will then complete the abovementioned RRI questionnaire regarding location, structure, and mechanism of the injury.

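### A running-related injury that coincides with quitting after the 6-week program can escape both the risk-factor and the cost analysis, because quitters' logs need not cover pain

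*Protocol article*

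**What the plan says.** **Log after the program** (Web-based training log after the 6-week STR program). "After the 6-week STR program, a digital training log is sent to the participants every two weeks". For people still running, "pain registration and monitoring of overuse injuries is similar to the methods used in the first six weeks". For people who stop, "Participants who quit running after the STR program can indicate so, and only have to complete the information on other sports activities".

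**Log during the program** (Web-based training log during the 6-week STR program). "When a training session is skipped, the reason for it will be asked (running-related pain, other pain, illness, motivation, or other reason". If the reason is running-related pain, site and severity follow.

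**Where the reason for stopping is recorded** (Follow-up questionnaires). "In the follow-up questionnaires continuation and reasons for discontinuation of running will be monitored".

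**Use of those questionnaires** (Statistical analyses). Risk factors are to be identified from the baseline questionnaire and the log alone: "Data of the follow-up questionnaires will not be used for this purpose, because these data do not contribute to a pre-running risk-profile".

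**Injury details and costs** (Questionnaire for injured runners; RRI cost analysis). "When an RRI is registered in the web-based training log, a questionnaire will be automatically sent to the participant after two weeks". Costs are calculated from that questionnaire and its follow-ups.

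**Why quitting matters** (Background). "An important dropout reason from these programs is the occurrence of a running-related injury (RRI".

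**The concern.** Under the Injury definition, being unable to run because of running-related pain for at least a week is an RRI. Stopping because of pain is thus a central case of the outcome. After week 6 it is also the case in which the log, as described, no longer requires any pain item.

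The one place named for recording why a runner stopped after the program is the follow-up questionnaires, and the Cox model does not use them. The reason given for leaving them out concerns predictors, since they are not part of a pre-running profile. It says nothing about whether they hold outcome information.

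Missing events of this kind would not be random. If readiness to quit when hurt varies with motivation, previous sport or age, the share of RRIs missed varies with them too, and their hazard ratios shift. Post-program RRIs and their costs would be understated.

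The safeguards described do not clearly repair this. The sports physician's check covers about 10% of subjects who sustain an RRI, so it tests injuries already registered and cannot find missed ones. Multiple imputation does not help if an unreported RRI is read as no event.

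**Working it through.** **1. The plan's own figures (Sample size).** 6,000 × (1 − 0.20) = 4,800 at follow-up. 4,800 × 0.20 = 960 RRIs. At 10 RRIs per factor, 960 / 10 = 96 factors. These reproduce.

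**2. Which RRIs have a route into the analyses.**

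| Situation | Route into the Cox model | Route into costs |
|---|---|---|
| Stops for pain during the 6 weeks | Yes, skip reason with site and severity | Yes, once registered |
| RRI logged after week 6, then quits | Yes, already in the log | Yes, questionnaire every four weeks until recovery |
| Pain starts, or reaches one week, around the time of declaring quitting after week 6 | None stated | None stated |

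Only the third row is a gap. With a two-weekly log it mainly concerns the last log interval before quitting.

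**3. Which window applies.** Statistical analyses ends exposure for non-injured runners at the end of the program, and the program lasts six weeks. The same section speaks of several RRIs in one subject over the study period and takes the first, and RRI logging continues after week 6. The two statements are not reconciled. If the window closes at week 6, quitters after the program are outside it, apart from pain that starts in week 6 and needs week 7 to meet the one-week criterion.

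**4. Effect on a hazard ratio.** The protocol gives neither the share of RRIs missed nor the share of events after week 6, so both are assumptions. Let *s* be the share of all first RRIs that occur after week 6, and *m*₀ and *m*₁ the shares of those missed in two exposure groups. To a close approximation the observed hazard ratio is the true one multiplied by

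(1 − *s* × *m*₁) / (1 − *s* × *m*₀).

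With *m*₀ = 0.10 and *m*₁ = 0.30:

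| *s* | Calculation | Multiplier |
|---|---|---|
| 0 (window ends at week 6) | 1 / 1 | 1.00 |
| 0.25 | 0.925 / 0.975 | 0.95 |
| 0.50 | 0.85 / 0.95 | 0.89 |
| 1 | 0.70 / 0.90 | 0.78 |

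Equal losses in both groups give a multiplier of 1.00 whatever *s* is.

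**5. Effect on counts.** Apply a common loss *m* of 10% to 30% to the 960 expected RRIs, assuming the 20% incidence covers the whole log period. RRIs missed = 960 × *s* × *m*.

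| *s* | RRIs missed | Apparent incidence |
|---|---|---|
| 0.25 | 24 to 72 | 19.5% to 18.5% |
| 0.50 | 48 to 144 | 19.0% to 17.0% |
| 1 | 96 to 288 | 18.0% to 14.0% |

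Even at the extreme, 672 RRIs remain, enough for 67 factors at 10 each. The issue is bias, not the number of events.

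**The case against.** The strongest reply is that the literal text confines the problem. The quit option applies only after the program, exposure for non-injured runners ends with the program, and stops for pain during the program are recorded session by session. On that reading incidence loses essentially nothing by this route. This stands, but only for that reading. The reference to the study period and the continued RRI logging leave the window open, and the cost analysis is not limited to six weeks.

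Second, a reader might infer that RRIs which make people stop running are lost wholesale and counted as non-injured. The document does not support that. An RRI logged before quitting counts and triggers the injury questionnaire, and nothing says that declaring quitting ends that series. No sentence says how quitters are classified or censored.

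Third, the bar on follow-up questionnaires is stated for identifying risk factors, not for incidence, costs or dropout. Injury as a reason for stopping could still appear in the description of dropout. That is correct. But the description supplies no event to the Cox model, and costs still depend on registration in the log.

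Fourth, an article condenses item-level log content, and the quit screen may ask more than the summary sentence says. That is possible, but the sentence states a rule about what quitters need to complete, and pain is not part of it.

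Finally, counting questionnaire reasons as events has its own weakness. No onset date or one-week check is described, and on the schedule in Follow-up questionnaires the last interval for March starters runs from week 26 to week 52. This limits such data to a sensitivity analysis.

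**Conclusion.** The point holds in a limited form. An RRI that begins, or meets the one-week criterion, around the time a runner declares quitting after week 6 has no stated route into the risk-factor or cost analysis. Because injury is named as an important reason for dropout, the loss is informative. It can understate post-program RRIs and costs and, if the risk period extends beyond week 6, bias hazard ratios for factors related to quitting when hurt.

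The size cannot be derived from the document. It would be wrong to quote 0.78 as the expected distortion: that needs every event to be post-program as well as the assumed 10% versus 30% loss. If a quarter to a half of events are post-program, the same losses give 0.95 to 0.89. With a window closing at week 6 there is almost no effect on hazard ratios, and the cost gap remains.

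**What to change.** 1. **Log.** When a participant indicates quitting, show once the skip-reason item already used in the 6-week log (running-related pain, other pain, illness, motivation, other), with site, severity and start date. Keep the pain items in that participant's next log so that the one-week criterion can be judged.
2. **Risk window and censoring.** In Statistical analyses, reconcile the end of the program with the study period, and state that runners without an RRI are censored at their last running exposure. Censoring alone does not recover a missed RRI, so item 1 is still needed.
3. **Sensitivity analysis.** Use injury-related discontinuation from the follow-up questionnaires as outcome information in a sensitivity analysis only, and keep those questionnaires out of the predictor set.

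The cost is one existing item and one extra set of pain questions for quitters, a slightly greater burden, plus a few sentences in the analysis section. The log change has to be in place before runners pass week 6, because the questionnaires as described give no onset date from which to reconstruct these events.
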